# The Effectiveness of a Lactobacilli-Based Probiotic Food Supplement on Bone Mineral Density and Bone Metabolism in Australian Early Postmenopausal Women: Protocol for a Double-Blind Randomized Placebo-Controlled Trial

**DOI:** 10.3390/nu16081150

**Published:** 2024-04-12

**Keywords:** study protocol, gut microbiota, postmenopausal women, probiotics, lactobacillus, bone mineral density

## Abstract

Osteoporosis affects one in three women over the age of 50 and results in fragility fractures. Oestrogen deficiency during and after menopause exacerbates bone loss, accounting for higher prevalence of fragility fractures in women. The gut microbiota (GM) has been proposed as a key regulator of bone health, as it performs vital functions such as immune regulation and biosynthesis of vitamins. Therefore, GM modulation via probiotic supplementation has been proposed as a target for potential therapeutic intervention to reduce bone loss. While promising results have been observed in mouse model studies, translation into human trials is limited. Here, we present the study protocol for a double-blind randomized controlled trial that aims to examine the effectiveness of three lactobacilli strains on volumetric bone mineral density (vBMD), trabecular, and cortical microstructure, as measured using High Resolution peripheral Quantitative Computed Tomography (HR-pQCT). The trial will randomize 124 healthy early postmenopausal women (up to 8 years from menopause) to receive either probiotic or placebo administered once daily for 12 months. Secondary outcomes will investigate the probiotics’ effects on areal BMD and specific mechanistic biomarkers, including bone metabolism and inflammatory markers. The trial is registered with Australian New Zealand Clinical Trials Registry (ACTRN12621000810819).

## 1. Introduction

Osteoporosis affects one in three women and one in five men over the age of 50 worldwide [1]. Increasing life expectancy in developed countries has brought osteoporosis and its clinical consequence, fragility fractures, into focus as a significant public health challenge [2]. Women in particular experience a pronounced rate of bone loss estimated to be 2–2.5% annually during the first five years following menopause [3,4], which then decreases to 1–2% annually a decade after menopause [5,6]. This rapid bone loss, primarily due to oestrogen deficiency post-menopause, is a key factor in the lower bone mass and heightened fracture risk observed in women compared to men [3]. The deficiency promotes osteoclastogenesis, leading to a negative imbalance in bone remodelling. Consequently, there is a progressive decline in bone mineral density (BMD) at critical osteoporotic fracture sites, including the lumbar vertebrae in the spine, femoral neck, and forearm [7].

Key lifestyle factors, particularly inadequate dietary intake of essential micronutrients, specifically calcium and vitamin D, are major contributors to bone loss [8]. Additionally, Vitamin K_2_ plays a significant role in bone metabolism [9,10,11,12], since it is essential for the γ-carboxylation of osteocalcin, a process crucial for bone formation and bone mineralization. Vitamin K is also synthesized by gut bacteria [13], underscoring the importance of gut microbiota in bone health. The human gastrointestinal tract’s microbiota performs vital functions, including immune regulation, maintenance of the gut barrier integrity, intestinal endocrine signalling, protection against pathogen overgrowth, and biosynthesis of vitamins, such as vitamin K_2_ [14,15]. These functions are integral to overall physiological health, including bone metabolism.

Pharmacological treatments for osteoporosis, while effective [16], suffer from low adherence, possibly due to fear of rare side effects [17] or complex dosage requirements [18]. This underscores the importance of exploring non-pharmacological options in preventing bone loss and reducing the risk of fragility fractures.

Recent evidence suggests that changes in the composition of gut microbiota through probiotic supplementation may favourably alter bone mass [19,20,21,22]. For example, in animal studies, a selected mixture of three probiotic strains (*Lactobacillus paracasei* DSM 13434, *Lactobacillus plantarum* DSM 15312, and *Lactobacillus plantarum* DSM 15313) [23] protected ovariectomized mice from ovariectomy-induced bone loss [20]. However, human clinical trials investigating the effect of probiotic supplementation on BMD are inconsistent. In a Swedish study [19], postmenopausal women receiving a similar probiotic *Lactobacillus* mixture experienced reduced areal BMD (aBMD) at lumbar spine, but no benefits at other sites, measured with dual energy X-ray absorptiometry (DXA), compared to placebo. Conversely, a different probiotic strain supplement administered to older (75–80 years old) postmenopausal women, showed increased volumetric BMD (vBMD) (measured with high-resolution peripheral quantitative computed tomography (HR-pQCT)) at the distal tibia, compared to the placebo [21].

To the best of our knowledge, there are only five clinical trials that have investigated the effectiveness of probiotic supplementation on BMD in postmenopausal women [19,21,24,25,26] to date. Their findings were assessed in two systematic literature reviews [27,28] that reported modest improvements in BMD at the lumbar spine, but no changes at other skeletal sites (particularly hip BMD). Only one trial examined vBMD using the highly sensitive HR-pQCT measure [25], whereas the remaining five studies measured aBMD via dual-energy X-ray absorptiometry (DEXA), a less sensitive but more widely available bone mineral density assessment method. Furthermore, inconsistencies in the existing evidence could be attributed to variations in probiotic strains, intervention durations (6–12 months), diversity in reported bone density measures, participants’ age (mean age ranging from 51–76 years), years from menopause (up to 12 years or more), underpowered or low sample sizes, and discrepancies both in reported bone turnover markers (BTM) and other primary biomarkers (what was measured in the findings reported).

To address these variations in the evidence, the current study examines a probiotic using a combination of strains with demonstrated efficacy in both a mouse model [23] and a human trial in postmenopausal women [19], utilises a 12-month intervention period, and employs aBMD, vBMD, and bone microstructure measurement techniques synergically. We specifically focus on early postmenopausal women (i.e., up to 8 years from menopause) to target the period of most rapid bone loss [3], examining a range of hormonal, inflammatory, and bone metabolism biomarkers, alongside changes in gut microbiota composition. The current study contributes to this emerging field by examining specific mechanistic biomarkers in early postmenopausal women.

Therefore, the primary aim of the study is to assess the effect of a probiotic containing three lactobacilli strains *Lactiplantibacillus plantarum* HEAL9 (HEAL9™), *Lactiplantibacillus plantarum* HEAL19, and *Lacticaseibacillus paracasei* 8700:2 (previously identified as *Lactobacillus paracasei* DSM 13434, *Lactobacillus plantarum* DSM 15312, and *Lactobacillus plantarum* DSM 15313) once daily for 12 months on vBMD in healthy early postmenopausal women, compared to a control group that will receive a placebo. Secondary aims are to assess changes between groups over 12 months in aBMD, gut microbiota composition, blood biomarkers (including bone metabolism and turnover markers, inflammatory markers), and dietary intake. The expected intervention effect is proposed to be mediated by beneficial changes in gut microbiota composition that stimulate bone formation, suppress osteoclast differentiation, and reduce inflammation, as well as improve markers of bone mineralisation, including calciotropic hormones and increased gut production of vitamin K_2_.

The study hypothesizes that supplementation with this specific probiotic once daily for 12 months will have more favourable effects on vBMD, aBMD, and bone metabolism, compared to the placebo. This effect is expected to be mediated by beneficial changes in gut microbiota composition (i.e., shift in bacterial diversity) and a consequent production of molecules that impact bone mineralization, calcium metabolism, osteoclastogenesis, and immune function inflammation (i.e., lower inflammatory biomarkers).

## 2. Materials and Methods

### 2.1. Study Design

The design is a double-blind randomized controlled trial that examines the effectiveness of a probiotic supplement, containing three Lactobacillus strains, versus placebo in a 1:1 ratio in healthy early postmenopausal women. The product will be taken daily for 12 months. This study was approved by the La Trobe University Human Research Ethics Committee (HREC 21038) and will be conducted at the Food, Nutrition and Dietetics Research Laboratory located at La Trobe University, Bundoora, Australia. The protocol was designed according to Standard Protocol Items: Recommendations for Intervention Trials (SPIRIT). Trial registration: Australia & New Zealand Clinical Trials Registry (ACTRN12621000810819).

### 2.2. Participants

Healthy early postmenopausal women between the ages of 45–65 years will be recruited to participate. Participants must have a minimum of at least one year since their last menstruation to meet the definition of menopause, and a maximum of up to eight years since menopause to meet the definition of early menopause. Participants will be eligible to participate in the study if they are a non-smoker, not taking hormone replacement therapy (or menopausal hormone treatment) for at least 12 months, have a body mass index (BMI) of between ≥18 and ≤32 kg/m^2^, and have maintained stable body weight for at least six months. The exclusion criteria include: a history of bone disease or any medical conditions that influence bone health or inflammation, such as hypothyroidism, inflammatory bowel disease, and rheumatoid arthritis; malignancy within the last five years; any systematic medication such as glucocorticoids; or consumption of more than four standard units of alcohol per day or more than five cups of coffee per day. Women will be further assessed at screening and eligible for enrolment with a T-score of >−2.5 at the total hip or lumbar spine (L1–L4) as measured using DEXA. If a screened participant’s T-score is ≤−2.5, this participant will be referred to their health practitioner for further investigation. Participants must be willing to give informed consent. Study visits will take place at La Trobe University, Bundoora, VIC, Australia, as well as the Austin Repatriation Hospital, Heidelberg, VIC, Australia. The study will be advertised by several methods, including distribution amongst professional networks (to staff and students at La Trobe University), email lists, and via targeted social media advertising circulated via platforms including Facebook, Instagram, and Twitter. Refer to Figure 1 for the recruitment process.

### 2.3. Randomization and Blinding

A computer-generated 10-block randomization list assigned study IDs sequentially to group allocations. An independent researcher, not involved in the trial, used this list to determine the probiotic group assignment. This randomization list was then provided to the manufacturer of the product (not involved in data collection) to box and label the product (either probiotic or placebo) in sequentially numbered containers. Each container was identical regardless of group allocation. These identical boxes were then provided to the research team. Neither the researchers nor the participants were aware of the group allocation. Participants will be assigned a study ID in the order of enrolment. The probiotic and placebo will have identical appearance and flavour.

### 2.4. Intervention

The active investigational product (IP) is a combination of the three probiotic bacteria *Lactiplantibacillus plantarum* HEAL9 (HEAL9™), *Lactiplantibacillus plantarum* HEAL19, and *Lacticaseibacillus paracasei* 8700:2, delivered in a capsule containing a powder with freeze-dried bacteria and maltodextrin used as filler. Each bacterial strain is equally represented, and the total bacterial dose is 1 × 10^10^ CFU/capsule to be taken daily for 12 months with water (food optional). The placebo capsules will have the same visual appearance with the same taste and texture as the active IP, with the exception that the probiotic powder is substituted with some yeast peptone. Adherence to intake will be evaluated by counting the number of unused capsules returned.

### 2.5. Restrictions during the Study

Participants will be asked to refrain from using other products containing probiotic bacteria, maintain stable body weight during the study (defined as weight changes that do not exceed ±5 kg), be fasting overnight (10 h) before all clinic visits including baseline (water allowed, but alcohol not allowed within 24 h prior to visit), refrain from strenuous exercise (defined as greater than 70% of the maximal pulse rate for one hour or more, or 24 h prior to and during the day of each clinic visit). Caffeine consumption must be limited to five cups of coffee, or corresponding amount of other caffeine-containing products, per day throughout the study period. Participants must refrain from smoking or use of nicotine-containing products, blood or plasma donations, or using calcium or vitamin D supplements or hormonal therapy for the study duration. Participants will be instructed to maintain their current physical activity habits throughout the duration of the study, unless their healthcare providers advise them differently. Once enrolled, participants who no longer meet the inclusion criteria or who can no longer comply with the restrictions will be terminated from the study. Unblinding will not take place until after the analysis is complete, even for participants who have terminated early.

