Additional bone mineral density measures include changes in aBMD measured by a trained DEXA researcher at the following sites: spine (L1–L4), total hip, femoral neck, and forearm, using a Hologic DXA machine (Time points: 0, 6, and 12 months). Following the manufacturer’s and standard guidelines, the non-dominant hip and forearm will be assessed using DXA. In the presence of disorders such as fragility fractures in the non-dominant site, the opposite site will be scanned. All scans will be analysed by one person to minimize intra-operator errors. A study that will assess the coefficient of variation in DXA measurements will be performed using 30 participants scanned twice. Calcaneal (heel) measurements will be carried out using quantitative ultrasound (QUS, Achilles, Abingdon, UK) and measured at time points: 0, 6, and 12 months.

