All statistical analyses will be performed using the SPSS statistical analysis software version 29 for Windows. Both Per-Protocol (PP), and Intention-to-Treat (ITT) analyses will take place. Per-protocol analysis will compare treatment groups, including only those study participants who completed the treatment that was originally allocated to them. Adherence to the intervention will also be taken into consideration in the per-protocol analysis by identifying and excluding potential non-adherent study participants from the analysis. All reported *p*-values will be two-tailed, while the level of statistical significance will be set at *p* < 0.05.

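### Terminating women from the study when they cease to meet the inclusion criteria or restrictions loses their only post-baseline primary scan and pulls the ITT analysis towards the per-protocol set

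*Protocol article*

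**What the plan says.** Section 2.5 of the protocol article sets the rule: "Once enrolled, participants who no longer meet the inclusion criteria or who can no longer comply with the restrictions will be terminated from the study". The following sentence mentions early-terminated participants only to say that they are not unblinded before the analysis is complete.

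The rule reaches two sets of conditions:

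- **Inclusion criteria (Section 2.2).** Age: "Healthy early postmenopausal women between the ages of 45–65 years will be recruited to participate". Time since menopause: "a maximum of up to eight years since menopause to meet the definition of early menopause". There is also a BMI range, and a DXA condition worded as "Women will be further assessed at screening and eligible for enrolment with a T-score of >−2.5 at the total hip or lumbar spine".
- **Restrictions (Section 2.5).** These include keeping weight within ±5 kg and not using calcium or vitamin D supplements or hormonal therapy during the study.

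Section 2.6.1 and Table 1 place the primary HR-pQCT scan at 0 and 12 months only. Section 2.8 states: "Both Per-Protocol (PP), and Intention-to-Treat (ITT) analyses will take place". It describes the per-protocol set as women who completed their allocated treatment, with non-adherent women excluded, and it names repeated-measures analysis of variance as the main model.

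The adverse-event paragraph at the end of Section 2.6.6 says that a woman may continue if the event is judged not to be caused by the intervention. It does not say what happens to her follow-up otherwise. Nowhere does the article say that a terminated woman is still scanned at 12 months.

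**The concern.** An ITT comparison keeps every randomised woman in her allocated group, whatever happens afterwards. A rule that re-applies entry conditions after randomisation and then ends follow-up works against this. Because there is no intermediate HR-pQCT scan, each termination before month 12 removes all information on that woman's primary change.

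Two things are at stake. The first is precision: evaluable numbers fall for reasons unrelated to whether a woman would have attended. The second is comparability: some triggers can be related to bone or to general health. A woman who starts calcium, vitamin D or hormonal therapy may do so because of symptoms or bone findings, and weight change can itself be linked to bone change. Losing those women is not safely ignorable.

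The two analysis sets also lose their contrast. Women excluded from the per-protocol set for a deviation would, under this rule, be missing from the ITT data as well. Repeated-measures ANOVA normally uses only women with complete data, which adds to the effect.

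**Working it through.** **1. The plan's own figure.** Inputs from Section 2.7: difference 1%, SD 1.78%, power 80%, type I error 0.05 (two-tailed, Section 2.8).

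n per arm = 2 × 1.78² × (1.960 + 0.842)² / 1² = 49.7, rounded up to 50. This reproduces the stated 50. Allowing for 20% drop-out, 100 / 0.8 = 125, against the stated 124. The sample size is consistent with its inputs.

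**2. Evaluable women under the plan.** 62 × 0.8 = 49.6 per arm. Two-sample t-test power with d = 1/1.78 = 0.562 (noncentral t) is 79.1%. The normal approximation gives 79.9%.

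**3. What the rule could add.** The article gives no expected termination rate, so the extra loss t is an assumption. Evaluable n per arm = 49.6 × (1 − t).

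| Extra loss t (assumed) | n per arm | Power (noncentral t) |
|---|---|---|
| 0 (terminations fall within the 20%) | 49.6 | 79.1% |
| 5% | 47.1 | 77.0% |
| 1/14 = 7% | 46.1 | 76.0% |
| 1/7 = 14% | 42.5 | 72.6% |

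The 1/7 row takes the eight-year limit literally. If years since menopause at enrolment are uniform over 1 to 8 (assumption), one woman in seven passes eight years during the 12 months: 124 / 7 ≈ 18 women. The 1/14 row assumes that status is checked only at visits, so that a woman crossing between months 6 and 12 is identified when her final scan is already due.

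If all 62 women per arm were scanned, power would be 87.4%, assuming the effect is not diluted.

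**4. The T-score route.** A simulation applied a −2.5 threshold at 6 months under these assumptions:

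- baseline T-score mean −1 (SD 0.9) or −1.5 (SD 0.7), all above −2.5 at entry;
- 6-month T-score change of −0.10 on placebo and −0.05 on probiotic, SD 0.2;
- correlation 0.3 or 0.6 with vBMD change;
- true vBMD difference 1.0 percentage point.

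It removed about 2.1% of placebo and 1.6% of probiotic women in the first setting, and 4.1% and 3.1% in the second. The estimated difference moved by 0.01 percentage points or less.

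**5. Which routes matter.**

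- *Time alone (age, years since menopause).* Under blinding these should be balanced between arms. They cost precision and narrow the population.
- *Weight change, supplements, hormonal therapy.* These happen after randomisation and may be related to outcome. The documents give no figures from which to size the bias.
- *T-score.* Negligible on the simulation, and probably not a continuing criterion at all.

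**The case against.** **ITT remains possible.** A reader might infer that the rule makes ITT analysis impossible. The documents do not support that. Women can still be analysed as randomised, with missing 12-month values handled under stated assumptions, and the methods may sit in an analysis plan or full protocol that is not shown. This stands. What does not follow is that those methods repair the problem: they replace outcomes by assumptions, and a scan not taken cannot be recovered.

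**The T-score is a screening test.** A reader might also infer that women are removed because they lost bone. Section 2.2 ties the threshold to screening and enrolment, and Table 1 lists the eligibility check in the screening phase only. The threshold concerns DXA areal BMD, a secondary outcome. Read literally, "eligible for enrolment with a T-score of >−2.5 at the total hip or lumbar spine" may need only one site above the limit. Removing the 5% of placebo women with the greatest loss, at correlation 0.5, would shift the placebo mean by 0.5 × 0.103 / 0.95 × 1.78 ≈ 0.10 points. But that removes women from one arm only, and by amount of loss. Crossing a fixed threshold depends mainly on the baseline T-score and happens in both arms. This objection stands, and the T-score should not carry the argument.

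**Age and years since menopause may be meant for entry only.** This is plausible: the article accepts an approximate year of cessation (Section 4), which could hardly be policed by the month. But Section 2.5 speaks of women already enrolled who no longer meet the criteria, so the wording points the other way.

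**The 20% allowance may cover terminations.** Section 2.7 excludes no cause of drop-out. If it covers them, nothing is lost against the planned power. This stands as to power. It does not answer the loss of observed ITT outcomes.

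**Conclusion.** The point holds as a conflict between a stated conduct rule and a stated analysis. Following Section 2.5 as written forfeits the only post-baseline primary measurement of every woman terminated before month 12. The promised ITT analysis is compromised rather than ruled out: it cannot rest on observed primary outcomes for all randomised women, and it moves towards the per-protocol set.

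The size is uncertain because the article gives no termination rate. Power is about 79% if terminations lie within the 20% allowance, and about 77% or 73% if an extra 5% or 14% are lost on top. The 14% depends on a uniform spread of years since menopause, literal use of the eight-year limit, and losses additional to ordinary drop-out.

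The possibility of bias rests on removal for weight change or for supplement or hormone use, and it cannot be quantified from the documents.

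**What to change.** Reconcile Sections 2.2, 2.5, 2.6.1, 2.8 and the adverse-event paragraph of Section 2.6.6:

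1. State that eligibility criteria such as age, years since menopause and T-score apply at enrolment.
2. Separate stopping the product from leaving follow-up. Whether and when the product is stopped is for the sponsor and is not prescribed here.
3. Invite all randomised women who still consent to the remaining visits, including the 12-month HR-pQCT. Record deviations from the restrictions and handle them in the per-protocol analysis.

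The cost is an amendment of about a paragraph and the already scheduled visits for women who would otherwise have been removed. Keeping women who deviated may dilute the ITT effect somewhat, and the per-protocol analysis is there to show that. The article describes the trial as ongoing, so the change is worth making before more 12-month scans are missed.

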#### 2.6.3. Blood Biomarker Measurements

Blood samples will be drawn using standard sterile IV venipuncture techniques by a trained phlebotomist. All samples will be obtained from a vein in the antecubital fossa of the arm using standard phlebotomy procedures. Plasma and serum samples will be decanted and aliquoted into de-identifiable labelled tubes and stored in a −80 °C freezer for subsequent analysis. Serum and plasma will be processed, stored, and assayed in the La Trobe Nutrition Clinical Trial Laboratory. Deidentified samples will also be sent to accredited private pathology laboratories for further analyses for the measurement of the concentrations of blood biomarkers (Time points: 0, 6, and 12 months). The analyses of serum or plasma for all other biomarkers will be conducted after data collection is complete, using standardised procedures and assays. This includes bone formation (Procollagen type 1 N propeptide (P1NP), total and undercarboxylated osteocalcin) and blood–bone resorption (Serum type I collagen cross-linked C-Telopeptide (CTx) or Tartrate-resistant acid phosphatase 5b (TRAP 5b)); osteoclast differentiation molecules osteoprotegerin (OPG) and receptor activator of nuclear factor kappa-Β ligand (RANKL); calciotropic hormones 25-hydroxy vitamin D, 1,25-hydroxy vitamin D, parathyroid hormone (PTH), and calcitonin; renal and liver function markers to assess normal function; and inflammatory markers high sensitivity C-reaction protein (hsCRP) and interleukin-6 (IL-6).

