Participants will be instructed to report adverse events at the time of event. If it is determined that the intervention is not causative of the adverse event, the participant will be allowed to maintain their participation in the study. Further assessment of any adverse events will be examined as to whether these differ between intervention and control groups.

Table 1 below shows an overview of study data collection and time points.

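### The unblinding rule is sound for routine use but, as worded, also bars releasing one woman's allocation when her medical care needs it

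*Protocol article*

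**What the plan says.** The rule is the last sentence of Section 2.5 of the protocol article (Restrictions during the Study): "Unblinding will not take place until after the analysis is complete, even for participants who have terminated early". It directly follows a sentence under which women who stop meeting the inclusion criteria, or who can no longer keep to the restrictions, are taken out of the study.

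Three other places bear on it:

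- **Section 2.3 (Randomization and Blinding)** says that researchers and participants are blinded and shows who has had the list: "An independent researcher, not involved in the trial, used this list to determine the probiotic group assignment" and "This randomization list was then provided to the manufacturer of the product (not involved in data collection". It describes no route by which an allocation could be released.
- **The adverse-event paragraph at the end of Section 2.6.6** makes continued participation depend on a causality judgement: "If it is determined that the intervention is not causative of the adverse event, the participant will be allowed to maintain their participation". It does not mention unblinding.
- **Section 2.4 (Intervention)** gives the contents of the arms. The active product is "delivered in a capsule containing a powder with freeze-dried bacteria and maltodextrin used as filler"; the placebo is the same in appearance, taste and texture "with the exception that the probiotic powder is substituted with some yeast peptone".

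**The concern.** The sentence in Section 2.5 is a fixed rule with an end date, no exception, and an explicit extension to women who have left. Staff who receive a clinician's request would have only that sentence to go by in this article, and followed literally it tells them to refuse.

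At stake is the care of an individual woman in an unusual case. The arms differ in content, so allocation could be relevant after a suspected reaction to something present in only one of them. It could also be relevant if lactobacilli grew from a normally sterile site, since women on active product take such bacteria daily. The information would exist and could be given to one clinician without touching the trial's outcome data.

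**Working it through.** The question is one of wording, so the check sets the relevant statements side by side. The article gives no figure to reproduce.

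1. **Is there another statement on unblinding?** Sections 2.3, 2.5, 2.6.6 and 2.8 and Table 1 are where one would expect it. Section 2.3 covers who is blinded and who received the list. The adverse-event paragraph covers reporting, causality and a comparison between groups. Section 2.8 and Table 1 do not address it. The sentence in Section 2.5 stands alone.

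2. **Does the sentence carry a qualifier?** No. It does not say 'routine', and it names no medical or emergency exception. The clause on early leavers widens a rule that already covers everyone.

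3. **When does the ban end?** When the analysis is complete. Most blood assays come after the last visit: "The analyses of serum or plasma for all other biomarkers will be conducted after data collection is complete". A woman who has an event during her 12 months of dosing is therefore always inside the ban. Its exact length is not a useful measure of harm, because an urgent need arises within hours or days.

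4. **Does the ban reach a woman who leaves after a product-related event?** Only by inference. The adverse-event paragraph says that a woman may stay if the product is judged not to be the cause. The converse, that she may otherwise leave, is implied. Section 2.5 names only eligibility and compliance as grounds for termination. She is nonetheless covered by the general ban, whether or not she counts as having terminated early.

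5. **Could allocation inform care?** The stated difference between the arms is probiotic powder against yeast peptone. Knowing the arm would narrow the candidates after a suspected reaction. It would not always settle the matter: Section 2.4 does not say whether maltodextrin or the capsule shell is common to both arms, and a clinician can treat the woman as if she had taken active product.

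6. **What would a release cost the blinding if it leaked?** This measures the cost of the fix, not the harm of the present rule. Inputs: 1:1 allocation (Section 2.1), and "A computer-generated 10-block randomization list assigned study IDs sequentially to group allocations", where '10-block' may mean blocks of 10 or 10 blocks. The second reading gives 124/10 = 12.4, so about 12 per block. Assume balanced blocks and a guesser who knows the block boundaries. The chance that another woman in the block is in the opposite arm, against 50% with no leak, is:
   - block of 10: 5/9 = 55.6%
   - block of 12: 6/11 = 54.5%

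   The expected gain in correct guesses is 9 × (5/9 − 1/2) = 0.5 in the first case and 11 × (6/11 − 1/2) = 0.5 in the second. Either way that is half a guess among the other 124 − 1 = 123 women.

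**The case against.** The strongest case against is that this is a missing code-break procedure under another name. A journal article commonly leaves emergency procedures to the full protocol, which is not shown. The position of the sentence also favours a harmless reading: coming straight after the termination rule, it most naturally says that a woman who leaves is not told her arm on the way out. The clinical stakes are low as well. This is a food-supplement probiotic in healthy women, the ingredients named for both arms are known, and in most events stopping the capsules would be enough.

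Most of this stands. The harmless reading is probably the intended one, and the stakes are low. The part that does not stand is the claim of mere silence. Had the article said nothing, an unseen procedure could fill the gap and there would be no point to raise. Instead it states a ban without exception, and a medical release described elsewhere would contradict that sentence as printed.

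A reader might go further in three ways that the document does not support:

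- **That the trial has no emergency code break, or means to refuse one.** The article does not show this; the full protocol may contain such a route.
- **That Section 2.5 expressly covers women who leave because of a product-related event.** Step 4 of the working shows that this is inferred.
- **That participants face a material risk.** No event rate is given, and nothing in the article shows that a case is likely.

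**Conclusion.** The point holds as a minor matter of patient safety: the only sentence on unblinding is broader than it needs to be and, taken literally, bars a medically needed release for one woman. Its size cannot be put in numbers. The article gives no event rate and none is assumed here; such cases would be rare and may never occur. The estimate, type I error and power are not affected.

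The conclusion rests on two things: that the sentence is read as printed, and that allocation would sometimes help a clinician. The second is plausible from the stated contents of the arms, but the article does not demonstrate it.

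**What to change.** Limit the ban to routine unblinding and add a narrow medical exception. Suggested text:

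> *Allocations will not be disclosed routinely before the analysis has been completed, and this includes women who leave the study early. One participant's allocation may be released to her treating clinician when her medical care requires it. A designated code holder outside the study team makes and logs the release. It is withheld from staff who scan, assay or analyse, and her data stay in the intention-to-treat analysis.*

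The text costs a few sentences and changes neither the sample size nor the analysis. It brings one real task. Section 2.3 shows that the independent researcher and the manufacturer have both had the list but does not say who keeps it, so one of them must be designated and be reachable throughout the study. The downside for blinding is small: a leaked allocation would move guesses within its block from 50% to about 55%, which is reason enough to limit disclosure to the clinician.
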